### Objective

This study aims to inform health policy in Ireland and internationally by conducting a mixed-methods study examining how key workers might enhance integration between primary and secondary care to improve outcomes for patients with FEP. Outcomes of interest include general and mental health outcomes, substance use disorders, and chronic illness and multimorbidity prevalence. We will examine the feasibility, acceptability, and likely efficacy of a key worker–led intervention in a *real-world* clinical setting, thereby informing future definitive interventions in the area.

## Methods

This project design was informed by the *MRC Framework for the Design and Evaluation of Complex Interventions to Improve Health* [70], which suggests the phased development of health interventions. The study design involved a mixed methodology in primary and secondary care in Ireland, with 2 sequential phases.

### Study Design and Setting

A longitudinal pre-post intervention in 8 general practices in 2 regions in Ireland (one urban and one rural), in which patients with FEP, will be identified from clinical records in general practice (using a previously developed software tool [71]) and in mental health services. Baseline and follow-up data (at 6 months) will be collected on a number of measures of patients’ physical and mental health.

### Intervention Development and Design

Semistructured interviews will be conducted with GPs and health care professionals, such as psychiatrists and nurses, working in mental health services (n=16) to inform the *complex intervention* which will consist of the following:

Academic detailing.Education and training of GPs.Key worker:To optimize (bidirectional) communication between primary and secondary care with regard to physical health issues requiring follow-up.To deliver brief interventions for problem alcohol use/tobacco smoking.To identify community-based health agencies (eg, primary care team members, nongovernmental organizations, and third sector) who can assist with preventative health interventions (see Figure 1).

**Figure 1 figure1:**
[figure not shown]
Key worker intervention.

### Approach to Sampling and Recruitment

The clinical lead in each of Ireland’s mental health service catchment areas will be invited to participate, and expressions of interest will be sought to participate in this feasibility study. From these expressions of interest, one urban and one rural service will be identified.

At both sites, all general practices will be eligible to participate in the study. From those who express an interest in participating, 4 practices will be selected using stratified sampling, to be representative in terms of practice size and location. Sampled GPs will be contacted about their participation, given further information on the study (eg, what their involvement will entail), and consulted about patient recruitment. The research team will telephone those not replying. Each practice will be visited by the principal investigator/lead researcher and provided with information about the research program.

At each participating practice, all patients who have been diagnosed with *FEP* in the preceding 4 years will be identified from clinical records (at the general practice or at the mental health service) and invited to participate in the study. Potential participants will be given written information on the study. Those interested in participating will be invited to meet a researcher who will be at the practice during the recruitment period. At this meeting, interested patients will be given further information on the study and will have an opportunity to ask the researcher questions. If they consent to participate, patients will be asked to sign a consent form. In total, 8 participants will be selected to participate from each practice (see Figure 2).

**Figure 2 figure2:**
[figure not shown]
CONSORT diagram—practice and patient recruitment.

### Sample Size

Semistructured interviews will be conducted with 16 health care professionals working in mental health services (n=16) to inform the *complex intervention*. Although it is difficult to predict the number of participants required to reach data saturation, our previous qualitative work [72,73] has indicated that 12 to 16 verbatim are required.

The goal of this feasibility study is to estimate rates of recruitment, consent, retention and response, methodological procedures, and issues. In addition, estimation of the parameters of likely primary outcome measures would allow the sample size of a definitive trial to be determined. With an average of 2 patients presenting to a GP with an FEP each year [74], that is, 8 per 4 years, and 8 practices in total across the 2 sites, we consider the sample size will be sufficient to estimate the actual recruitment and retention rates for a sample of patients recruited in primary care and provide data on acceptability of study processes and outcome measures which will inform a future definitive trial.

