## Introduction

### Background

Psychosis is a clinical syndrome that affects several domains, including affective, cognitive, motivational, sensory, and social functioning. Psychosis can manifest in a variety of symptoms including positive symptoms (eg, delusions and hallucinations), negative symptoms (eg, reductions in motivation, volition, and emotion experience or expression), declines in cognitive and social functioning, and disorganized speech and behavior [1]. Psychosis often manifests as a symptom of psychotic-spectrum disorders, which include schizophrenia-spectrum disorders (eg, schizophrenia and schizoaffective disorder) and affective disorders with psychotic features (eg, bipolar disorder with psychotic features) [2]. Psychotic-spectrum disorders are associated with severe difficulties in psychiatric, physical, and functional well-being. Each year it is estimated that 1500 people develop a first episode of psychosis in Ireland. The implications of this issue for population health are considerable. Psychosis usually develops in late adolescence or early adulthood, a critical phase of our life cycle in terms of personal, academic, and economic development. In addition, the personal, familial, and societal costs of psychosis are considerable [3-7].

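### The case rate behind the sample size is not reconciled with the protocol's own national incidence, and it leaves no margin for the fixed quota of 8 patients per practice

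*Protocol article*

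**What the plan says.** The Sample Size section takes its patient numbers from a cited source: "With an average of 2 patients presenting to a GP with an FEP each year [74], that is, 8 per 4 years, and 8 practices". On this basis alone it concludes: "we consider the sample size will be sufficient to estimate the actual recruitment and retention rates". It sets no target precision for those rates.

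Approach to Sampling and Recruitment defines the pool by diagnosis: "all patients who have been diagnosed with *FEP* in the preceding 4 years will be identified from clinical records". The records searched are those of the practice or of the mental health service. The section then fixes the number enrolled: "In total, 8 participants will be selected to participate from each practice". Practices are chosen in each of the two areas as follows: "4 practices will be selected using stratified sampling, to be representative in terms of practice size and location".

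The Background section gives the only national figure: "Each year it is estimated that 1500 people develop a first episode of psychosis in Ireland".

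The Data Analysis section defines the patient recruitment rate as the percentage of those invited who take part.

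**The concern.** Two figures in one protocol describe how common first-episode psychosis is, and nothing connects them. The rate used for planning is stated per GP but multiplied out per practice. It counts people presenting to a GP, whereas the study enrols people who have been diagnosed. Presentations could include suspected or repeated cases that cannot be enrolled as separate participants. The document does not say what its source counted.

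There is also no slack. Even at the stated rate, the expected number of cases in a practice (8) equals the number to be enrolled (8). If the true rate is lower by any amount, an average practice cannot fill the quota, whatever the consent rate. At stake are the size of the sample and the precision of the recruitment and retention estimates, which are the study's stated purpose and are meant to inform a definitive trial.

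**Working it through.** **Inputs from the protocol**
- Planning rate: 2 patients per GP per year (Sample Size).
- Look-back window: 4 years (Approach to Sampling and Recruitment).
- Practices: 8, four in each of two areas (Sample Size; Approach to Sampling and Recruitment).
- Quota: 8 participants per practice (Approach to Sampling and Recruitment).
- National incidence: 1500 new cases a year (Background).

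**Inputs not in the protocol, assumed and shown as ranges**
- Practices in Ireland: 750 to 2000.
- Population: 4.5 to 5.5 million, used only to put the 750 in context.
- Retention: about 80%, used only to illustrate precision.

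**Step 1. Reproduce the plan's figure.** 2 per year × 4 years = 8, and 8 × 8 practices = 64. This treats one GP as one practice. The quota gives the same total, 8 × 8 = 64, so the required uptake is 64/64 = 100%.

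**Step 2. Compare with the national figure.** If each new case is counted at exactly one GP, the number of GPs at which the two figures agree is 1500/2 = 750. With the rate applied per practice, the number of practices is 1500 × 4/8 = 750. At 4.5 to 5.5 million people, 750 units would each serve 4,500,000/750 = 6000 to 5,500,000/750 ≈ 7300 people.

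**Step 3. Expected pool under the national figure.** Cases per average practice over 4 years = 1500 × 4 / practices = 6000 / practices. Multiply by 8 for the study, and divide 64 by that total for the overstatement.

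| Assumed practices in Ireland | Cases per practice, 4 years | Total over 8 practices | Overstatement (64 / total) |
|---|---|---|---|
| 750 | 8.0 | 64 | 1.0 |
| 1000 | 6.0 | 48 | 1.3 |
| 1500 | 4.0 | 32 | 2.0 |
| 2000 | 3.0 | 24 | 2.7 |

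**Step 4. GPs or practices.** Let U be the number of GPs nationally and g the number of GPs per practice. The pool is (1500/U) × 4 × 8 × g, which depends only on U/g, the number of practices if g is the same nationally as in the study. With U = 1500 and g = 2 the pool is 64, because U/g = 750. With U = 2500 and g = 3 it is 57.6, because U/g ≈ 833. Multi-GP practices restore the planned figure only as far as they bring the practice count back towards 750.

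**Step 5. Precision.** The 95% Wilson half-width is z√(p(1−p)/n + z²/4n²) / (1 + z²/n), with z = 1.96 and p taken at the whole-number count nearest 80%. Every eligible patient is assumed to be enrolled, and clustering by practice is ignored.
- n = 64 (51 retained): 0.097, about 10 points.
- n = 48 (38 retained): 0.113, about 11 points.
- n = 32 (26 retained): 0.132, about 13 points.
- n = 24 (19 retained): 0.156, about 16 points.

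**The case against.** The strongest reply is that the size of any discrepancy cannot be established from the protocol. No section gives the number of GPs or practices in Ireland, or the number of GPs in a study practice. A reader might infer that the pool is probably overstated about two-fold, or that a typical practice does not hold 8 diagnosed patients. Neither follows. Two-fold is a single point on an assumed range, and at 750 practices there is no overstatement. This objection stands.

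A reader might also infer that a shortfall would be mistaken for poor recruitment. The Data Analysis section rules that out for the recruitment rate, because its denominator is patients invited. Fewer cases widen the interval but do not by themselves lower the rate. Nor does any section say that the assumed rate will be carried into the definitive trial. Both objections stand.

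The two figures may also both be true. One counts people who develop the illness and the other counts presentations, so patients seen by more than one GP would allow more than 750 GPs. One urban and one rural area need not match a national average. This weakens any claim of outright contradiction, but it does not rescue the sample-size argument. If presentations exceed individuals, they are the wrong count for a pool of diagnosed patients. Searching mental health service records does not enlarge the expected pool either, since the national figure already covers new cases wherever they are seen.

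Finally, no precision threshold is stated, so a smaller sample cannot be shown to breach one. That is correct, and the half-widths above show only what is lost.

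**Conclusion.** The point holds as an unreconciled planning input. The only case rate offered for sufficiency agrees with the protocol's own incidence at about 750 GPs or practices nationally, if each case is counted once. It also moves from GP to practice and from presentation to diagnosis without explanation. Over an assumed 750 to 2000 practices, the expected pool is 64 down to 24, an overstatement of 1.0 to 2.7 times. Because the quota equals the expected pool, any overstatement puts the quota out of reach in an average practice.

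The consequence is loss of precision: for retention near 80%, a half-width of about 10 points at 64 patients becomes about 13 at 32 and 16 at 24. These are best-case figures that assume complete identification and consent. The documents do not support a particular overstatement factor, a biased recruitment rate, or failure against a stated criterion. The change is worth making because it costs little and bears directly on what the study is meant to estimate.

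**What to change.** - **Sample Size:** state whether the rate is per GP or per practice, and whether it counts presentations or diagnosed individuals. Reconcile it with the 1500 new cases a year in the Background section. Give the expected number of diagnosed patients per practice as a range, with the resulting total for 8 practices and the precision of the recruitment and retention rates at that total.
- **Approach to Sampling and Recruitment:** replace the fixed quota with all eligible consenting patients, up to 8 per practice.
- **Data Analysis:** add the number of diagnosed patients found per practice and per 1000 registered patients, taken from the records search already planned, so that the definitive trial can be designed on an observed rate.

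The cost is wording in two sections and one extra descriptive measure, which needs the registered list size of each practice. No additional patients are required. The drawback is that the stated expected sample and precision become less favourable.

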### Ethical Considerations

Ethical considerations and safeguards include the following:

Informed consent and consenting capacity: all potential participants (GPs and patients) will be given written information on the study and the model of care being proposed and will be asked to provide written consent that they are happy to participate and that nonparticipation will not compromise their usual care. Participation in the study will be on a voluntary basis. No inducements to participate will be offered.Confidentiality: Any data/personal details that could potentially reveal the identity of individuals will be removed. Only anonymized, deidentified information will leave the practice of origin. To allow follow-up, an alphanumeric code will be assigned to each participant’s data; a database will be maintained on a password-protected database. The list will be kept separately from patient data but will indicate the medical record number of each participant and the alphanumeric code. All research data will be stored on a password-protected desktop computer at the host organization. Study participants will be invited to give permission to have their name, address, and contact details held by the research team to facilitate their receiving a synopsis of the study findings on publication and to be contacted for follow-up data collection. All data will be stored securely at the host institution.Clinical governance does no harm: it is possible that participating in the study may raise health-related issues for participants and may identify a health issue that requires clinical intervention. Therefore, all participants will be advised to speak with their doctor if participating in the study has raised any such issues. Furthermore, only patients who health care professionals deem able to participate will be asked to take part.General Data Protection Regulation (GDPR): GDPR compliance will be adhered to in terms of the following:Data privacy rights—participants will have the right to request information about their data throughout the research process.Transfer of data—participants will be informed about the circumstances under which their data may be transferred and safety measures which will be taken to protect the data (eg, data are encoded).Retention of data—patients will be informed how long their data will be stored.

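### Eight participants per practice equals the plan's whole expected eligible pool; if practices have several GPs, the same figure is a quota that caps the recruitment rate

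*Protocol article*

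**What the plan says.** The Sample Size section starts from "With an average of 2 patients presenting to a GP with an FEP each year [74], that is, 8 per 4 years", combines this with "8 practices in total across the 2 sites", and concludes: "we consider the sample size will be sufficient to estimate the actual recruitment and retention rates".

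The section Approach to Sampling and Recruitment takes 4 practices at each of the two sites. It uses the same window: "all patients who have been diagnosed with *FEP* in the preceding 4 years will be identified from clinical records", at the practice or at the mental health service, and these patients are invited. It then says: "In total, 8 participants will be selected to participate from each practice".

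Ethical Considerations adds two steps that reduce numbers. Participation is voluntary, and "only patients who health care professionals deem able to participate will be asked to take part". Data Analysis defines the patient recruitment rate as the share of invited patients who take part. No expected value is given for approval, consent or retention, and no number of GPs per practice.

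**The concern.** The figure 8 does two jobs. In the Sample Size section it is the expected number of patients who presented over 4 years. In the sampling section it is the number to be enrolled per practice. If both refer to the same practice, enrolment uses up the whole pool and nothing is left for missed records, clinician exclusion or refusal. The rate is also quoted per GP but multiplied by practices, so the true size of the pool is unclear.

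The study's stated goal is to estimate recruitment, consent, retention and response, and to supply parameters for a definitive trial. If the pool is 8, fewer patients than stated will be available for retention and outcome parameters. If the pool is larger, the recruitment rate as defined may reflect the quota rather than patients' willingness. Either way, a headline feasibility result is harder to interpret.

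**Working it through.** **Inputs from the protocol article.** Rate: 2 per GP per year (Sample Size). Window: 4 years (Sample Size; Approach to Sampling and Recruitment). Practices: 4 per site x 2 sites = 8. Enrolment: 8 per practice. Approval and consent proportions: not given. GPs per practice: not given.

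**Step 1: the plan's own figure.** 2 x 4 = 8 per 4 years, which reproduces the printed figure.

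**Step 2: pool against enrolment, with the rate used per practice as the plan uses it.**
- Expected pool: 8 x 8 practices = 64.
- Planned enrolment: 8 x 8 practices = 64. This total is derived; it is not printed in the text.
- Required uptake: 64 / 64 = 100%, through identification, clinician approval and consent together.

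**Step 3: how sensitive this is.** Suppose a practice has exactly 8 eligible patients, each enrolling independently with probability u (an assumption). The chance that the practice reaches 8 is u^8:
- u = 0.9: 43%
- u = 0.8: 17%
- u = 0.5: 0.4%

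Expected enrolment from 64 is 64u:

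| Overall uptake (assumed) | Expected enrolment |
|---|---|
| 90% | 57.6 |
| 70% | 44.8 |
| 50% | 32.0 |
| 30% | 19.2 |

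The 8 is also an average. If the pool per practice varies as a Poisson count with mean 8 (an assumption), a practice has at least 8 eligible patients with probability 0.547. All eight practices do so with probability 0.547^8, about 0.008, even if everyone enrols.

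**Step 4: the rate read per individual GP.** With g GPs in a practice, the pool is 8g and the uptake needed for 8 participants is 8 / 8g = 1/g. If all identified patients are invited and exactly 8 are taken, the recruitment rate defined in Data Analysis cannot exceed the same fraction:

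| GPs per practice (assumed) | Expected pool per practice | Highest possible recruitment rate |
|---|---|---|
| 1 | 8 | 100% |
| 2 | 16 | 50% |
| 3 | 24 | 33% |
| 4 | 32 | 25% |

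At g = 3, a practice where every invited patient consents and one where a third consent would both report 33%. If clinicians exclude some patients before invitation, the denominator shrinks and the ceiling rises accordingly, but it remains a ceiling set by the quota whenever more than 8 are invited.

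**The case against.** The strongest reply is that practices often have more than one GP. They are chosen "4 practices will be selected using stratified sampling, to be representative in terms of practice size and location", the rate is per GP, and the word for taking the 8 is selection, which suggests a larger group to choose from. Patients may also be found through the mental health service, so the pool need not be limited to those who presented to a GP. Figure 2, to which the enrolment sentence refers, is not available and may show invited and enrolled numbers separately.

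This stands as far as it goes. A reader might infer that the target can be reached only with complete uptake; the documents support that only if the per-GP rate is used per practice. Nor does the plan state an expected recruitment rate of 100%; that value is implied by its figures. But the multi-GP reading does not repair the text. The unit is still unconverted, and the fixed 8 becomes the ceiling shown in Step 4.

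It is also true that the recruitment rate can be estimated at any uptake when 8 is not a binding quota, since its denominator is those invited. A shortfall would then be a feasibility result in itself. What a shortfall undermines is the claim of sufficiency for retention and outcome parameters.

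Three further inferences are tempting and should not be drawn:
- **National incidence.** The Background says "Each year it is estimated that 1500 people develop a first episode of psychosis in Ireland". At 2 per GP per year, 1500 / 2 = 750 GPs would account for every case. That contradicts the rate only if the number of GPs in Ireland is known, and the documents do not give it.
- **Missing precision.** The article gives no confidence interval widths and no allowance for clustering by practice. A condensed article may leave these to the full protocol or analysis plan, so their absence is not a fault here.
- **A clustering penalty at 8 per practice.** Inflating the variance for 8 patients per practice would assume the very enrolment that the plan's inputs do not deliver.

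**Conclusion.** The concern holds in a conditional form with two branches, and the text needs correcting in both.

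- **Rate used per practice, as the plan does:** planned enrolment of 64 equals the expected pool of 64. This requires 100% uptake despite clinician screening and voluntary consent. At an assumed 30-70% overall uptake, about 19 to 45 would enrol.
- **Rate read per GP, with g GPs per practice:** full uptake is not needed, but selecting 8 from all those invited caps the recruitment rate at 1/g, or 50% at g = 2 and 33% at g = 3.

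The pool and enrolment figures rest only on the plan's own inputs. The uptake range, the values of g and the Poisson model are assumptions. Figure 2 could clarify what the 8 means, but the two sections as worded do not. The documents do not establish that 64 is unattainable; they establish that the stated inputs do not support it.

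**What to change.** Revise the Sample Size and sampling sections as follows.

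1. State whether the rate of 2 per year is per GP or per practice, and give the number of GPs in the selected practices, so that the expected pool per practice follows.
2. Present 8 per practice (64 in all, or the figure after conversion) as the expected number identified and invited, not enrolled.
3. Give expected enrolment over a stated uptake range. For example, 30-70% of 64 is 19.2 to 44.8, about 19-45. Limit the claim of sufficiency to that number.
4. Choose one of two rules. Either enrol all eligible patients who consent, or, if 8 is a cap, define the recruitment rate as the percentage of invited patients who consent, counted before selection. The second option also fits the Sample Size section, which names consent as a rate to be estimated.

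The cost is the rewording of two sections, plus one definition in Data Analysis if the cap is kept. No extra patients are needed. The downside is that the stated sample size looks less favourable. Dropping the cap also gives up a fixed upper limit on workload per practice; keeping it and counting consent before selection avoids that.
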